#### Functional resistance training

2.5.2

According to the weakness of lower limbs in ESRD patients, as well as the damage of external oblique muscle, internal oblique muscle, transverse muscle, and rectus abdominis muscle caused by Rutherford Morison incision and Alexandra incision in common operation methods of kidney transplantation, the following functional training is designed to strengthen the muscle strength reserve (Table 2). This process will be combined with breathing training at the same time, exhale when exerting, and inhale when relaxing, and each action is repeated 8 to 12 times. The training intensity is defined by self-perceived exertion (Borg11–13), and the frequency is 3 times a week (Figs. 2–7).

**Table 2 T2:** Functional resistance training.

Training action	Action diagram	Action points
Heel up	Figure 2	Hold the object by hand, keep your legs as wide as your shoulders, exhale and slowly lift your heels to the highest point to maintain 3–5 s (calm breathing here), then exhale and slowly land on your heels to relax.
Kick	Figure 3	Hold the object by hand, keep the legs as wide as the shoulder, one side of the lower limb bend the hip and knees, then keep the hip flexion and straighten the knee, and then extend the entire lower limb. Repeat this action alternately from left to right.
Squat up	Figure 4	Hold the object by hand, feet apart, shoulder wide, exhale with knee flexion not exceeding toe, the center of gravity sinking, maintain 3–5 s (calm breathing here), exhale and stand up and relax.
Dilatation of chest	Figure 5	Keep your arms straight, gradually raise your head forward and upward, and inhale deeply at the same time; then retract your arms and exhale deeply at the same time.
Bridge movement	Figure 6	Take a supine position, hands flat on both sides of the body, legs flexion, feet flat on the bed, arms lifted off the bed, maintain 3–5 s (calm breathing here), exhale, and relax.
Push the wall	Figure 7	Stand in the corner of the wall, back against one wall, push the other wall with the outside hand, maintain 3–5 s (breathe calmly here), relax and proceed alternately from side to side.

**Figure 2 F2:**
[figure not shown]
Heel up.

**Figure 3 F3:**
[figure not shown]
Kick.

**Figure 4 F4:**
[figure not shown]
Squat up.

**Figure 5 F5:**
[figure not shown]
Dilatation of chest.

**Figure 6 F6:**
[figure not shown]
Bridge movement.

**Figure 7 F7:**
[figure not shown]
Push the wall.

#### Flexibility training

2.5.3

After the end of aerobic exercise and resistance training, the stretch will be carried out for each resistance training muscle group (Table 3), the duration of each action is 20 s, which is repeated 2 to 3 times, the total time is 10 minutes, and even breathing is maintained during the whole course (Figs. 8–10).

**Table 3 T3:** Flexibility training.

Training action	Action diagram	Action points
Stretch the front of the leg	Figure 8	Hold the object with your hands, stand on one leg, grab the left foot with your left hand and pull it toward your buttocks. Keep the upper body as straight as possible (feet as close to the buttocks as possible) to maintain 20 s, 30 s, left, and right alternately.
Stretch the back of the leg	Figure 9	Bend your right leg, hold your left knee with both hands, straighten your left leg and hook your toes, bend your waist and back straight down, and maintain 20 s, 30 s, left, and right alternately.
Calf stretch	Figure 10	The right leg in front of the bow and arrow, the left toe forward, the body to do forward, downward elastic stretch, the left heel does not leave the ground, the total process 20–30 s.

**Figure 8 F8:**
[figure not shown]
Stretch the front of the leg.

**Figure 9 F9:**
[figure not shown]
Stretch the back of the leg.

**Figure 10 F10:**
[figure not shown]
Calf stretch.

### Study outcomes

2.6

#### Primary outcomes

2.6.1

1.Cardiopulmonary function: the cardiopulmonary function will be evaluated by 6MWT, and the maximum distance that the subjects can reach will be measured. The 6MWT is significantly correlated with peak oxygen consumption,^[17]^ which has good reliability and validity and can predict the adverse outcome of ESRD.^[18]^2.Physical fitness: physical fitness will be evaluated by grip strength, 4-meter gait speed and 5 chairs repeated standing tests (5R-STS). Grip strength and lower limb muscle strength are good indicators of systemic muscle strength and reliable predictors of increased risk of hospitalization and death.^[19]^

#### Secondary outcomes

2.6.2

1.Postoperative condition: the occurrence probability of postoperative complications, such as hospital stay, postoperative pulmonary infection and bleeding, postoperative drainage, and extubation time is recorded.2.Quality of life: the quality of life is evaluated by the SF-36, which includes physical function, limitation caused by the body, body pain, general health, vitality, social function, limitation caused by emotion, and mental health. The higher the comprehensive score, the better the quality of life.^[20]^3.Psychological evaluation: the HADS will be used to evaluate the emotional state of anxiety and depression. There are several problems of anxiety and depression respectively. The higher the total score, the more serious the anxiety or depression. This scale has good reliability and validity in our general hospitals.^[21]^

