We hypothesized that personalized family exercise programs for ESRD patients can optimize functional ability, confidence, and motivation during waiting before kidney transplantation, reduce postoperative complications, and optimize transplant results. In the present study, we aim to optimize the family exercise training on the functional ability of ESRD patients undergoing kidney transplantation, and to reduce the adverse effects of frailty, decreased cardiopulmonary function, and psychological dysfunction on the prognosis of kidney transplantation. Before a randomized control trial (RCT) can be conducted, a feasibility study is required to determine whether a larger trial is possible and if so the optimally designed features should be outlined. Therefore, we will conduct a single-center feasibility trial of a novel home-based exercise program in ERSD patients awaiting kidney transplantation. We expect to provide a scientific and valuable reference for the application of family exercise pre-rehabilitation in patients awaiting kidney transplantation.

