## Materials and methods

2

The proposed feasibility trial is a single-arm, single-center study of an ERAS-based home exercise pre-rehabilitation for patients listed for kidney transplantation. ESRD patients awaiting kidney transplantation will be selected as subjects to undergo personalized family exercise pre-rehabilitation, including aerobic exercise, functional resistance exercise, and flexibility training. Briefly, a 6-minute walking test (6MWT), 4-meter gait speed, grip strength, and sit-to-stand test will be used as the main outcome indicators. The effect of family exercise pre-rehabilitation on the optimization of body function in ESRD patients undergoing kidney transplantation will be assessed. The days of hospitalization after kidney transplantation, postoperative complications, health survey (the Short Form Health Survey, SF-36), and the Hospital Anxiety and Depression Scale (HADS) will be used as secondary outcome indicators to evaluate the improvement of quality of life, psychological function, and postoperative rehabilitation of patients after kidney transplantation. These indexes will be collected before and after intervention (baseline and before kidney transplantation), before discharge (after kidney transplantation), and 1 month after discharge. In addition, age, sex, race, type of occupation, marital status, education, body mass index (BMI), duration of dialysis, causes of ESRD, and types of renal replacement therapy should be recorded. A study schema is provided in Figure 1.

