### Statistical analysis

2.11

SPSS24.0 statistical software and Office Excel 2016 will be used to analyze the test data. The quantitative data will be tested by the Kolmogorov–Smirnov test to determine whether they are following a normal distribution. Quantitative data: if the comparison before and after the intervention follows the normal distribution, the paired sample *t* test will be used; if it does not meet the normal distribution, the non-parametric test Wilcoxon symbolic rank test will be used for analysis. The results are expressed as mean ± standard deviation (
$\bar{X}\pm S$
). The postoperative hospitalization days, postoperative complications, postoperative drainage, and extubation are compared with the previous data in the hospital. If the data satisfies normal distribution, an independent sample *t* test will be used; otherwise, the Mann–Whitney *U* test is used for analysis, and the results are all expressed as mean ± standard deviation (
$\bar{X}\pm S$
). The qualitative data will be analyzed by chi-square test (χ^2^ test), and the results are expressed as a percentage (%). The level of significance is *P* < .05.

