## Discussion

3

With the increasing number of renal transplant operations, the continuous maturity of surgical methods, and the pursuit of better clinical outcomes, people's interest in the ERAS program has greatly increased. Pre-rehabilitation before operation can improve the baseline function of patients, enhance surgical tolerance, and reduce postoperative complications.

When waiting for renal transplantation, ESRD patients often show frailty and decreased cardiopulmonary function, leading to increased complications and mortality after renal transplantation. Preoperative pre-rehabilitation can optimize the health status of individuals before the operation. Therefore, patients can achieve better results after operation. The family based pre-rehabilitation exercise program has been proved to be effective in heart surgery, liver transplantation, and other related fields. The family sports plan is simple, and the subjects are easy to grasp the essentials of their movements, including walking, strength training, and other sports, which do not need professional equipment and are not affected by the venue, weather, and other factors. Pre-rehabilitation exercise programs for renal transplantation in the family can reduce the time and economic burden brought by dialysis patients going to the rehabilitation clinic regularly. In the present trial, we, for the first time, will assess an ERAS-based home exercise pre-rehabilitation in patients listed for kidney transplantation.

In the present study, participants will record their activities in their sports diaries and report them in WeChat groups. In a larger RCT, real-time data collection can be considered. Physiotherapists can monitor the compliance and progress of the exercise program every day and avoid reporting bias by participants.

Both objective and subjective parameters will be included in the primary and secondary outcomes. We should not only pay attention to the objective incidence of hospital stay and postoperative complications but also consider the impact on the patient-based HRQoL. Patients can return to family and society in the best state by improving HRQoL, embodying the core of diagnosis and treatment in the concept of ERAS, which is centered on serving patients.

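### The postoperative complication outcome is defined inconsistently and is assigned to the wrong data type in the statistical analysis

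*Protocol article*

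**What the plan says.** Section 2.6.2 (Secondary outcomes), under the item on postoperative condition, states that "the occurrence probability of postoperative complications, such as hospital stay, postoperative pulmonary infection and bleeding, postoperative drainage, and extubation time is recorded".

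Section 2 (Materials and methods), like the Abstract, gives stay and complications as separate secondary outcomes: "The days of hospitalization after kidney transplantation, postoperative complications, health survey (the Short Form Health Survey, SF-36" and so on.

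Section 2.11 (Statistical analysis) names four separate items and their comparator: "The postoperative hospitalization days, postoperative complications, postoperative drainage, and extubation are compared with the previous data in the hospital". For that group, "If the data satisfies normal distribution, an independent sample *t* test will be used; otherwise, the Mann–Whitney" U test applies, and "the results are all expressed as mean ± standard deviation". The following sentence sends qualitative data to the chi-square test, "and the results are expressed as a percentage", without saying which outcomes count as qualitative.

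The hypothesis in the Introduction includes the aim to "reduce postoperative complications, and optimize transplant results". The Discussion speaks of the "objective incidence of hospital stay and postoperative complications".

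**The concern.** Two statements do not fit together. Section 2.6.2 treats complications as something with a probability of occurring, yet its examples mix events (pulmonary infection, bleeding) with items that are durations or amounts (hospital stay, drainage, extubation time). Section 2.11 separates these items again but then handles complications as if they were a measurement like the other three.

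At stake is what the complication result will mean. The trial compares its participants with earlier patients of the same hospital. If the definition mixes outcome types and the summary is a mean ± SD, a reader cannot be sure whether the reported number is the proportion of patients affected or an average count per patient, nor that the same thing was counted in both groups.

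**Working it through.** The documents give no complication rate and no sample-size figure for this outcome. The 47 in section 2.10 comes from a paired t test with effect size 0.37. It is used here only as a denominator, and as an upper limit, because not every enrolled patient need be transplanted. All complication counts below are assumptions for illustration.

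**1. The definition, side by side**

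- Section 2.6.2: stay, drainage and extubation time appear as examples of complications.
- Abstract and section 2: hospital days and complications are two outcomes.
- Section 2.11: hospital days, complications, drainage and extubation are four outcomes.

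Section 2.6.2 is therefore out of line with the rest of the article.

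**2. Which analysis rule applies**

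Section 2.11 names complications explicitly in the t test/Mann–Whitney group. The chi-square sentence names nothing. An analyst following the text literally uses the first rule and reports mean ± SD. That does not fit an occurrence probability.

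**3. What a mean ± SD would show**

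With mean = Σx/n and SD = √[(Σx² − n·mean²)/(n − 1)], take n = 47 and nine complications in total. Then mean = 9/47 = 0.19 and n·mean² = 81/47 = 1.723.

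- Case A, nine patients with one each: Σx² = 9, SD = √[(9 − 1.723)/46] = 0.40. Affected: 9/47 = 19.1%.
- Case B, three patients with three each: Σx² = 27, SD = √[(27 − 1.723)/46] = 0.74. Affected: 3/47 = 6.4%.
- Case C, four patients with 4, 3, 1 and 1: Σx² = 16 + 9 + 1 + 1 = 27, SD = 0.74. Affected: 4/47 = 8.5%.

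All three share the mean 0.19. Cases B and C share the SD as well, yet differ in the proportion affected. If counts per patient are analysed, mean ± SD does not determine that proportion.

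**4. If each patient is coded 0/1**

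The mean is then the rate. For 5, 9 or 14 affected of 47, mean ± SD is 0.11 ± 0.31, 0.19 ± 0.40 or 0.30 ± 0.46, against rates of 10.6%, 19.1% or 29.8%.

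The test hardly matters either. For an assumed 9/47 against an assumed 45/150 historical patients, chi-square without continuity correction is 197 × (9×105 − 38×45)² / (47×150×54×143) = 2.118, p = 0.146. The t test and the Mann–Whitney test on the same 0/1 data each give p = 0.147.

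**5. What the existing percentage rule would give**

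For 9/47, the Wilson 95% interval has centre (p + z²/2n)/(1 + z²/n) = (0.1915 + 0.0409)/1.0817 = 0.2148. Its half-width is z√[p(1 − p)/n + z²/4n²]/(1 + z²/n) = 1.96 × 0.0611/1.0817 = 0.1106. The result is 9/47, 19.1% (95% CI 10.4% to 32.5%), which states the rate and its uncertainty directly. For 5/47 and 14/47 the intervals are 4.6% to 22.6% and 18.7% to 44.0%.

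**The case against.** The strongest reply is that this is awkward English rather than a faulty plan. The item in section 2.6.2 is headed postoperative condition, under which stay, drainage and extubation time fit naturally, and the rest of the article keeps them apart from complications. Section 2.11 already contains the right method for yes/no data, and complications are the obvious postoperative candidate for it. If they are coded 0/1, the mean is the rate and the p-value is practically unchanged.

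Much of this stands, and it limits the point. A reader might infer that the plan yields no usable complication rate, or that every recipient would count as having a complication because each has a hospital stay. The documents do not support either reading: hospital days are listed separately in three places, pulmonary infection and bleeding are named as events, and a percentage rule exists.

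A reader might also fault the article for not saying which tube extubation refers to, or for not including graft loss and death. The first is an operational detail that an article may leave to the full protocol. The second would be a new endpoint: the hypothesis speaks only of transplant results in general.

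The reply does not remove the contradiction itself. Complications are named in the sentence on t and Mann–Whitney tests and are not named in the chi-square sentence, and 0/1 coding per patient is nowhere stated.

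**Conclusion.** The point holds as an inconsistency of definition and a wrong assignment of data type. Section 2.6.2 mixes quantitative outcomes with events, and section 2.11 sends complications to the quantitative rule although a suitable qualitative rule stands in its next sentence.

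The size depends on coding, which the article does not give. With 0/1 coding per patient, the rate survives and only its presentation suffers (0.19 ± 0.40 instead of 19.1%). With counts per patient, the same mean of 0.19 is compatible with 6.4%, 8.5% or 19.1% of patients affected in the assumed examples.

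The point is minor to moderate. Complications belong to the stated hypothesis, but they are a secondary outcome of a single-arm feasibility trial, and the primary functional outcomes are untouched.

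**What to change.** - In section 2.6.2, list postoperative hospital days, drainage and extubation time as separate quantitative outcomes. Define complications (pulmonary infection, bleeding) as a yes/no outcome per patient, read in the same way from participants' and historical records.
- In section 2.11, take complications out of the sentence on the t and Mann–Whitney tests and assign them by name to the existing chi-square and percentage rule. Report n, % and a confidence interval.

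The cost is small: edits to the wording and to the case-report form. No new method is needed.

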### Data collection

2.7

In addition to the data collection involving our primary and secondary outcomes, the information regarding patient demographics and clinical variables, such as age, sex, type of occupation, marital status, education, BMI, dialysis of history, and frequency, causes of ESRD, and type of renal replacement therapy, will be also collected. The above-mentioned features are selectively collected on the admission day (baseline), on the day before operation (second follow-up), on the discharge day (third follow-up), and 4 weeks post-operation (fourth follow-up). The proportion of patients who agree to participate in the trial and the reasons for disagreement will be summarized. Moreover, the number and percentage of participants who complete the complete exercise plan will be also recorded. Scheduled data collection at each time point is presented in Table 4.

**Table 4 T4:** Scheduled events and timeline of the trial.

	Study period					
	Time point	Enrollment	Preoperative	perioperative		Follow up
		12+ weeks before surgery	Before surgery or day of surgery	Discharge	1 month	
Enrollment	**Eligibility screening**	×				
	Informed consent	×				
Interventions	ERAS-based home exercise pre-rehabilitation		×			
Assessments	6MWT	×		×	×	×
	Grip strength	×		×	×	×
	4-meter gait speed	×		×	×	×
	5R-STS	×		×	×	×
	Postoperative condition				×	
	SF-36	×		×		×
	HADS	×		×		×

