### Inclusion criteria

2.3

The inclusion criteria will be set as follows:

1.ESRD patients are estimated to undergo kidney transplantation in more than 12 weeks, and the first kidney transplant is on the waiting list of the deceased donor in the Second Affiliated Hospital of Hainan Medical University;2.the age is 18 to 60 years old; and3.patients volunteer and sign the informed consent form.

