### Study intervention

2.5

All subjects will complete all baseline assessments by trained physiotherapists, who work out and demonstrate personalized exercise prescriptions for each patient according to the results of the functional evaluation, including aerobic exercise, resistance training, and flexibility training. Patients will be trained to correctly use self-perceived exertion (Borg) to monitor exercise intensity, distribute family exercise diaries, and exercise bracelets. In addition to dialysis treatment while waiting for kidney transplantation, the family exercise pre-rehabilitation needs to be completed until the patient returns to the hospital for kidney transplantation, and the functional ability, quality of life, and psychological function of all participants will be then re-evaluated. If the participants stop exercising for 1 week or several weeks due to illness, they can participate intermittently and record the disease and intermittent participation in the case report table, which will be explained in the data analysis.

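### Section 2.7 anchors the last visit to the operation where the abstract and section 2 anchor it to discharge, and it labels the admission day as baseline although baseline must precede the home programme

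*Protocol article*

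**What the plan says.** The protocol article describes its visit schedule in several places.

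- **Section 2.7, Data collection (text):** four time points, "on the admission day (baseline), on the day before operation (second follow-up), on the discharge day (third follow-up), and 4 weeks post-operation (fourth follow-up".
- **Section 2, Materials and methods, and in the same terms the abstract:** indexes are collected "before and after intervention (baseline and before kidney transplantation), before discharge (after kidney transplantation), and 1 month after discharge".
- **Section 2.5, Study intervention:** "All subjects will complete all baseline assessments by trained physiotherapists, who work out and demonstrate personalized exercise prescriptions" from the functional results. Later in the same section, "the family exercise pre-rehabilitation needs to be completed until the patient returns to the hospital for kidney transplantation", after which participants are assessed again.
- **Section 2.5.1, Table 1:** the walking prescription is calculated from heart rates and distance in the 6-minute walking test.
- **Section 2.3, Inclusion criteria:** "ESRD patients are estimated to undergo kidney transplantation in more than 12 weeks".
- **Table 4:** enrolment is labelled "12+ weeks before surgery". The pre-operative time point covers any time before surgery or the day itself. The last label is one month, with no statement of what the month is counted from.
- **Section 2.12:** adverse events are reported until 30 days after transplantation.

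**The concern.** Site staff would turn to section 2.7 to learn when to measure, and it differs from the rest of the article on two visits.

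For the last visit there are two incompatible starting points, the operation and discharge. Table 4 does not choose between them. Walking distance, grip strength, gait speed, chair stands, SF-36 and HADS may all change with time since surgery. Under the discharge anchor, a patient who stays longer has had more time since the operation when measured, and length of stay is a secondary outcome in its own right.

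For the first visit, the only hospital admission that the article describes is the one for transplantation, and the items that follow in the same sentence are the operation and discharge. Read that way, the measurement called baseline would be taken after the home exercise has ended. The trial has one arm, and the paired before-after comparison in section 2.11 is its planned test of functional change. There is no control group to fall back on if the first measurement is taken at the wrong time.

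**Working it through.** The documents state no figure for the size of this discrepancy, and the sample size of 47 does not enter into it. The check sets the definitions side by side and converts the two final-visit anchors to a common time scale.

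**1. Last visit**

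Inputs:
- 4 weeks = 28 days after the operation (section 2.7).
- 1 month = 28 to 31 days after discharge (abstract and section 2; the conversion of a month to days is mine).
- L = postoperative stay in days. The documents give no value, so the values below are assumptions.

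Formulas:
- Operation anchor: postoperative day 28.
- Discharge anchor: postoperative day L + 28 to L + 31.
- Gap: (L + 28 to L + 31) − 28 = L to L + 3 days.

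| Assumed stay L | Discharge-anchored visit (postoperative day) | Gap from day 28 |
|---|---|---|
| 7 | 35 to 38 | 7 to 10 days |
| 14 | 42 to 45 | 14 to 17 days |
| 21 | 49 to 52 | 21 to 24 days |
| 28 | 56 to 59 | 28 to 31 days |

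For stays of 7 to 21 days the visit therefore falls between day 35 and day 52, against day 28.

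Two further consequences follow:
- A day-28 visit lies inside the 30-day adverse-event period. A discharge-anchored visit lies outside it for any stay above 2 days, since L + 28 > 30 when L > 2.
- For a stay of 28 days or more, the operation-anchored visit would fall on or before the discharge visit, which section 2.7 lists as coming earlier.

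**2. Baseline**

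- Section 2.7: data are "selectively collected on the admission day (baseline".
- Section 2.5: baseline results come first and determine the prescription; return to hospital for the transplant ends the programme.
- Table 1: no walking target can be set without an earlier 6-minute walking test.
- Table 4: enrolment is 12 or more weeks before surgery.
- Section 2: "These indexes will be collected before and after intervention (baseline and before kidney transplantation".

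If admission means the transplant admission, the two readings of baseline are separated by the whole home-exercise period. That period is planned at more than 12 weeks. Its actual length is unknown, because eligibility rests on an estimate and the introduction calls the timing of transplantation unpredictable.

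**3. Pre-operative visit**

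Section 2.7 names the day before the operation. Table 4 allows any time before surgery or the same day. The first lies inside the second, so this is a narrower wording and not a contradiction. It still needs aligning, because all participants wait for a deceased donor and the day before surgery may not be available.

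Table 4's cross marks appear displaced in the text version, so only its labels are used here.

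**The case against.** The strongest reply concerns baseline. A reader might infer from section 2.7 that the before-after contrast is left open, or that the trial would compare two measurements taken after the programme and find a difference near zero whatever the true effect. The documents do not support that. The abstract, sections 2, 2.5, 2.5.1 and 2.11, and Table 4 all point to pre-intervention against pre-transplant, and the literal alternative could not be carried out, because the prescription needs a prior walking test. Admission can also loosely mean entry to the study. This reply stands: the intended contrast can be inferred. What remains is that the data-collection section names the wrong day on its plain reading.

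It can also be said that the sentence in section 2.7 follows a list of demographic and clinical variables and may refer only to those. The reference is indeed unclear. But the section opens with the primary and secondary outcomes, and a four-visit schedule ending after the operation is a natural timetable for outcomes and an odd one for sex or education.

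On the last visit, three points deserve weight. It plays no part in the baseline to pre-transplant comparison. With one arm, a shifting visit time cannot bias a comparison between arms. And discharge is a workable anchor if used consistently: it fixes the interval between the discharge and last visits, whereas the operation anchor leaves that interval at 28 − L days (21 days for a stay of 7, 7 days for a stay of 21). All three hold. None of them removes the contradiction between the two stated anchors.

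**Conclusion.** The point holds as an internal inconsistency on two visits.

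The last visit has two stated anchors and no reading reconciles them. They differ by the postoperative stay plus 0 to 3 days: about postoperative day 35 to 52 against day 28 if stays run from 7 to 21 days. The range rests on that assumed stay; the conflict itself does not. Under the discharge anchor, time since surgery at that visit varies with a secondary outcome.

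The admission-day baseline is a wording error with a recoverable intent. It does not show that the primary contrast is undefined, nor that the expected change would be about zero. It needs correction because the single-arm paired comparison depends on a measurement taken before exercise begins.

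This is not detail left to a fuller document. The article states incompatible definitions, and an analysis plan cannot afterwards repair visits held at different times.

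**What to change.** - In section 2.7, replace the admission day as baseline with enrolment, before the exercise prescription is issued.
- Use one anchor for the last visit in the abstract, section 2, section 2.7 and Table 4. Time since the operation is preferable, because it does not depend on length of stay and falls within the 30-day adverse-event period. This is a reasoned choice and not the only valid one; discharge would also serve if used throughout.
- If the operation anchor is chosen, say how the last two assessments are handled for a patient still in hospital at 4 weeks.
- Align the pre-operative wording in section 2.7 with Table 4, which allows before surgery or the day of surgery.
- Record the actual date of every assessment, so that time since surgery can be reported.

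The cost is wording in four places, with no new assessments. The small downside of the operation anchor is that the last visit may have to be booked independently of discharge. The change should be made before data collection.
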